**Methods:**

This is a multicenter prospective study that focuses on Chinese elderly patients with SCH who have TSH levels below 10 mU/L. After obtaining the informed consent of the patients, their initial diagnosis information will be registered, and they will be asked to fill out questionnaires such as the Montreal Cognitive Assessment-Basic (MoCA-B), Hamilton Depression Scale (HAMD), Hypothyroidism Symptom Questionnaire (SRQ), frail scale(FRAIL), fatigue scale, and EQ-5D. In addition, thyroid function tests, blood lipid analysis, carotid artery ultrasound, and thyroid ultrasound examinations will be conducted. Patients will also be grouped according to FT_4_ levels, the changes in FT_4_ and its relationship with TSH can also be described. For patients over 80 years old, a decrease in FT_4_ will be used as an endpoint event, while for patients between 60-80 years old, TSH levels greater than or equal to 10mIU/L or a decline in FT_4_ will be used as the endpoint event. The TSH reference intervals of the general and elderly populations will be used to calculate medical costs associated with multiple follow-ups of patients, and a social-economic analysis will also be conducted.

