### Research objectives and main results

The goal of this study is to prospectively follow up on elderly patients with SCH who are diagnosed using age-specific TSH reference intervals and non-age-specific TSH reference intervals, which aims to establish TSH reference intervals for different age groups to improve the diagnosis and management of SCH in the elderly. The main outcomes being assessed include thyroid function, hypothyroidism-related symptoms, cardiovascular events, cognition, depression, and fatigue, as well as economic and social benefits analysis. The above information will help make informed decisions about the best course of treatment for elderly patients with SCH.

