### Inclusion criteria and exclusion criteria

Inclusion criteria:

Elderly patients with SCH will be included according to the elderly and the general population-specific reference ranges, respectively.

(1) Inpatients and/or outpatients aged≥60 years.(2) The levels of free triiodothyronine(FT_3_) and FT_4_ are within the normal range.(3) TSH is greater than the upper limit of the normal reference range (old standard) and less than the upper limit of the normal reference range (new standard).

Exclusion criteria:

(1) Does not meet the inclusion criteria, does not sign the consent form, or participates involuntarily.(2) Exit halfway due to various reasons.(3) Unable to cooperate with the project team to complete all inspection contents.(4) Other factors leading to TSH increase. 1) increased TSH caused by measurement errors; 2) convalescence stage of the euthyroid sick syndrome; 3) central hypothyroidism; 4) renal insufficiency; 5) lack of glucocorticoids; 6) the recovery stage of thyroid function in subacute thyroiditis; 7) having taken amiodarone or lithium; 8) other interfering factors.

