### Study follow-up assessments

When a patient has FT_4_ levels below the lower limit of the normal reference range during follow-up, follow-up is terminated and thyroid hormone replacement therapy will be initiated. For patients aged 60 to 70 years, start treatment when TSH≥10mIU/L. For patients aged 71 to 80 years, treatment begins when TSH≥10 mIU/L and is accompanied by symptoms of hypothyroidism. Normal value reference ranges will be established based on the TSH levels of 120 normal elderly individuals over 60. Elderly SCH patients screened according to the TSH reference interval in the normal population and the elderly population will be followed up every 6 months, including the subclinical hypothyroidism questionnaire, the Montreal Cognitive Assessment-Basic (MoCA-B), Hamilton Depression Scale (HAMD), Hypothyroidism Symptom Questionnaire (SRQ), frail scale(FRAIL), fatigue scale, EQ-5D, thyroid function, blood lipid analysis, carotid color ultrasound, and thyroid ultrasound. The estimated sample size is 438. Patients diagnosed with different TSH reference intervals will be compared for cognitive function, depression scores, hypothyroidism, fatigue severity, carotid atherosclerosis, lipid profile, and cardiocerebrovascular complications. Besides, TSH reference intervals will be applied to calculate medical costs and evaluate the economic benefits of multiple follow-ups of patients with SCH. The research design can be seen in **Figure 1**.

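### Inclusion criterion 3, read literally, admits only patients between the two TSH limits and contradicts the planned comparison of patients diagnosed by each reference interval

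*Protocol article*

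**What the plan says.** The statements are all in the protocol article.

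- **Inclusion criteria and exclusion criteria, criterion 3.** TSH must lie above the upper limit of one range and below that of another, in the words "range (old standard) and less than the upper limit of the normal reference range (new standard". No numerical limits are given and neither standard is defined. Exclusion criterion 1 removes anyone who fails an inclusion criterion, so criterion 3 is binding.
- **Same section, introductory sentence.** "Elderly patients with SCH will be included according to the elderly and the general population-specific reference ranges, respectively".
- **Research objectives and main results.** The goal is to follow "elderly patients with SCH who are diagnosed using age-specific TSH reference intervals and non-age-specific TSH reference intervals".
- **Study follow-up assessments.** Patients screened by either interval are seen every 6 months, and "Patients diagnosed with different TSH reference intervals will be compared for cognitive function, depression scores, hypothyroidism, fatigue severity", among other outcomes. The estimated sample size is 438. The section adds: "Normal value reference ranges will be established based on the TSH levels of 120 normal elderly individuals over 60".
- **Abstract, Methods.** The population is "Chinese elderly patients with SCH who have TSH levels below 10 mU/L".
- **Introduction.** In the investigators' earlier survey of people over 65, SCH prevalence was 19.87% by the current interval and 3.3% by an age-specific one.

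**The concern.** SCH by the age-specific interval requires TSH above that interval's upper limit. Criterion 3 requires TSH below the new limit. If the new standard is the age-specific interval, the criterion shuts out one of the two groups that the objective and the planned comparison need.

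The study is meant to support an age-specific limit by showing that it picks out the patients who matter clinically. That needs outcomes on both sides of the limit. With patients on one side only, a low progression rate describes those patients but cannot show that patients above the limit fare differently.

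**Working it through.** **Step 1: which standard is which.** Write G for the general-population upper limit and E for the age-specific (elderly) upper limit. The fall in prevalence from 19.87% to 3.3% implies E > G. There are two possible readings of criterion 3:

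- old = G, new = E gives G < TSH < E, a non-empty band;
- old = E, new = G gives E < TSH < G, which no patient can satisfy when E > G.

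Only the first reading is workable.

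**Step 2: who is eligible.** With FT4 normal:

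- SCH by the general range: TSH > G
- SCH by the age-specific range: TSH > E
- Criterion 3: G < TSH < E

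Every eligible patient satisfies the first line. None satisfies the second, because TSH > E and TSH < E exclude each other.

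**Step 3: the statements side by side.**

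| Place | TSH range implied | Patients above E? |
|---|---|---|
| Criterion 3 | G to E | No |
| Introductory sentence to the criteria | SCH by either range | Yes |
| Research objectives and main results | SCH by either range | Yes |
| Study follow-up assessments | SCH by either range, compared | Yes |
| Abstract, Methods | SCH with TSH below 10 mU/L | Yes, if E is below 10 |

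Criterion 3 is the outlier, but it is the numbered rule by which a site would screen.

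**Step 4: size.** The total of 438 cannot be reproduced, because the article gives only the significance level of 0.05. It is taken here as given, and its missing derivation is not part of this point.

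- Criterion 3 as written: 438 between the limits, 0 above.
- All patients above G, at the survey prevalences:
  - between the limits: (19.87 − 3.3) / 19.87 = 83.4%; 438 × 0.834 ≈ 365
  - above E: 3.3 / 19.87 = 16.6%; 438 × 0.166 ≈ 73
- With the abstract's cap at 10, patients are lost only from the group above E. If half of that group were lost (an assumption; the article gives no figure), its share would be 0.083 / (0.834 + 0.083) = 9.06%. That is 438 × 0.0906 ≈ 40 patients, leaving about 398 between the limits.

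**Step 5: what 40 to 73 patients can carry.** The Introduction cites progression of 3.4% (3 years) and 26.8% (6 years) in earlier SCH cohorts. Taken only as a range:

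- 73 patients: 73 × 0.034 ≈ 2.5 to 73 × 0.268 ≈ 19.6 events
- 40 patients: 40 × 0.034 ≈ 1.4 to 40 × 0.268 ≈ 10.7 events

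At 26.8%, the 95% half-width is 1.96 × √(0.268 × 0.732 / n), or about 10 percentage points for n = 73 and 14 for n = 40. The upper group would exist, but its estimates would be imprecise.

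**The case against.** The strongest reply is loose drafting. The introductory sentence, the objective and the follow-up section all say that patients diagnosed by either range are included and followed, and the study-flow figure is not available in the text reviewed. This stands in part. It means that 438 versus 0 is the result of applying the criterion as written, not a known enrolment result. It does not remove the need to correct the criterion.

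A reader might infer more than the article supports:

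- **That eligibility rests on a limit not yet in existence.** The Introduction shows that an age-specific range was already in use in the earlier survey. The article does not say that the range from 120 normal individuals is the new standard, or that it is set after enrolment began. What can be said is that the limit used at enrolment is not identified.
- **That sensitivity and specificity are fixed at 0% or 100%.** Both ranges would be constant within the band as enrolled. But Research type mentions a diagnostic-test analysis without naming an index test or gold standard, Limitations plans an indicator combining T4 and TSH, and Data analysis recalculates the intervals from study data.
- **That overlapping groups will be tested as independent.** The article says only that they will be compared. Handling of nested groups can sit in the full protocol or analysis plan.
- **That every analysis fails.** Between-limit patients are exactly those whom the two rules label differently, so costs under each rule can be contrasted in them. Their absolute progression rate also bears directly on overdiagnosis.

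The 120 normal individuals do not fill the gap: they are a reference sample, not patients with SCH. Recalculating the limit might move a few enrolled patients above it, but that is not a planned comparison group.

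**Conclusion.** The contradiction holds and must be resolved. As written and binding, criterion 3 excludes every patient with SCH by the age-specific range, while the introductory sentence, the objective, the planned comparison and the abstract's bound describe a wider population. Applied literally, the outcome comparison between intervals cannot be made, and the study cannot show that the age-specific limit discriminates between patients who progress and those who do not. Description of the between-limit group, and of its costs under each rule, survives.

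The conclusion rests on reading old as general-population and new as age-specific, which the prevalence figures support. The split of about 365 and at most 73 further assumes that the over-65 survey distribution and its age-specific limit apply to hospital patients aged 60 and over, and that enrolment is unselected. The figure of 73 is an upper one because of the cap at 10. The article does not show that nobody above the age-specific limit was in fact enrolled.

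**What to change.** 1. Define both standards, with their numerical limits, and identify the age-specific limit applied at enrolment.
2. Reconcile criterion 3 with the abstract, the objective and the follow-up section: include TSH above the general-population upper limit and below 10 mIU/L.
3. Classify patients at baseline into two exclusive strata: (A) between the two limits; (B) above the age-specific limit. Make the between-interval comparisons A versus B.
4. State that stratum B will be small, and report its estimates with confidence intervals.

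If enrolment is still open, this costs one amended criterion, two definitions and a sentence on strata, with the total of 438 unchanged. The price is fewer between-limit patients (about 365 to 398 instead of 438) and imprecise estimates in B.

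Study population gives enrolment as December 2022 to December 2023. If it is complete, rewording cannot add stratum B. If patients above the age-specific limit were enrolled, correct the criterion to match what was done and report the strata. If only the band was enrolled, drop the between-interval comparison and the claims about the limit's discrimination, and report a single-group cohort of between-limit patients.

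### Three statements of TSH eligibility define three different populations, and one of them would let patients aged 60-80 enter with the TSH endpoint already met

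*Protocol article*

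**What the plan says.** The protocol article describes who enters in three places.

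- **Abstract, Methods:** the study concerns "Chinese elderly patients with SCH who have TSH levels below 10 mU/L".
- **Inclusion criteria and exclusion criteria, lead sentence:** "Elderly patients with SCH will be included according to the elderly and the general population-specific reference ranges, respectively". No TSH ceiling is attached.
- **Same section, criterion 3:** TSH must exceed the upper limit by the old standard and be "less than the upper limit of the normal reference range (new standard"). Neither limit is given a number. Study follow-up assessments says that reference ranges will be established from 120 normal people over 60.

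Other provisions bear on the consequence.

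- Criterion 2 at entry: "The levels of free triiodothyronine(FT_3_) and FT_4_ are within the normal range".
- The endpoint at ages 60-80, from the abstract: "TSH levels greater than or equal to 10mIU/L or a decline in FT_4_ will be used as the endpoint event". Over age 80 only a fall in FT4 counts.
- Study follow-up assessments: "For patients aged 60 to 70 years, start treatment when TSH≥10mIU/L". At 71-80 the TSH trigger also requires symptoms.
- Data analysis plans a Cox model for survival results and does not name the contrast.

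The abstract's Discussion, Research objectives and main results, and Study follow-up assessments all describe following, and in places comparing, patients diagnosed under both intervals.

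**The concern.** A site working from the numbered criteria never meets the abstract's cap of 10, and cannot tell whether a patient above the age-specific limit is eligible. The lead sentence admits that patient and criterion 3 rejects the same patient.

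Two things are at stake. First, if criterion 3 is applied literally, the group diagnosed by the elderly range is empty and the planned comparison between intervals cannot be made. Second, if the lead sentence is applied without the abstract's cap, a patient aged 60-80 with TSH of 10 or more meets the endpoint on the day of entry and contributes no time at risk. One aged 60-70 also meets the stated treatment trigger, so there is no untreated course to observe. Unless the new limit lies above 10, all such patients fall in the group above it. Any comparison of progression across that limit would then partly restate the entry TSH.

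**Working it through.** **Step 1. The statements side by side.**

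| Statement | Lower TSH bound | Upper TSH bound | Patients above the new limit enter? | TSH ≥10 possible at entry? |
|---|---|---|---|---|
| Abstract | as implied by SCH | 10 | yes, up to 10 | no |
| Lead sentence of the criteria | general or elderly limit | none | yes | yes |
| Criterion 3 | old limit | new limit (no value) | no | only if the new limit exceeds 10 |

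No two rows describe the same population.

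**Step 2. Who could have an event at time zero.** FT4 must be normal at entry, so an FT4 below the reference range cannot be present at baseline. Over age 80, TSH is not an endpoint. That leaves patients aged 60-80 with TSH ≥10, and only under the lead sentence, or under criterion 3 with a new limit above 10.

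**Step 3. Can the number be derived?** No. The documents give neither limit, no TSH distribution and no age split. The sample size of 438 comes without design inputs, so it cannot be reproduced, and the point does not depend on it. What follows is illustration only.

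Inputs from the Introduction: SCH prevalence over age 65 of 19.87% by the current range and 3.3% by the age-specific range. Assumptions: TSH is log-normal with log-scale SD σ, these prevalences can be read as upper tails of TSH, and the old limit is 4.0-5.0 mIU/L.

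- z(19.87%) = 0.846; z(3.3%) = 1.838; difference 0.992.
- New limit = old limit × exp(0.992σ).
- P(TSH ≥10) = 1 − Φ(0.846 + ln(10/old)/σ).
- Share of all patients above the old limit = P / 0.1987.

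*Criterion 3 alone.* For σ from 0.4 to 0.7 the new limit runs from 5.95 (old 4.0, σ 0.4) to 10.01 (old 5.0, σ 0.7). It reaches 10 only when σ = ln(10/old)/0.992, which is 0.92, 0.81 or 0.70 for old limits of 4.0, 4.5 or 5.0. Over this range criterion 3 admits essentially nobody at TSH ≥10.

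*Lead sentence, abstract's cap ignored.*

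| Assumed inputs | P(TSH ≥10) | Share of those above old limit | Of 438 |
|---|---|---|---|
| old 4.0, σ 0.4 | 0.085% | 0.4% | 2 |
| old 5.0, new 7 (σ = ln(7/5)/0.992 = 0.339) | 0.19% | 1.0% | 4 |
| old 4.0, new 9 (σ = ln(9/4)/0.992 = 0.817) | 2.46% | 12.4% | 54 |
| old 5.0, σ 0.7 | 3.31% | 16.7% | 73 |

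These counts cover all ages, so they overstate day-0 events by the unknown share over 80. They also ignore the FT4 entry condition and apply a city survey to hospital inpatients and outpatients.

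*The group that criterion 3 removes.* If the survey proportions carried over, 3.3/19.87 = 16.6% of patients above the old limit would lie above the new one, about 73 of 438. Read literally, criterion 3 makes that group zero.

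**Step 4. After reconciliation.** With a cap of TSH below 10 at the qualifying measurement, TSH-defined events at that measurement are zero by construction.

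**The case against.** The strongest reply is that the cap is in the document. The abstract's sentence is a plain statement of the study population, and a reader who applies it gets no TSH events at entry. Criterion 3 is itself a ceiling: with any new limit of 7-9 it admits nobody at 10 or above. The lead sentence merely introduces the numbered criteria and can be read as limited by them. This is also a condensed article whose study-process figure is not available here.

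Much of this stands. A reader might infer that the plan creates time-zero events and so builds in the finding that the new limit separates progressors from non-progressors. The documents do not support that. It requires setting aside the abstract's cap and letting the lead sentence override a numbered criterion. It also assumes an above-versus-below contrast in the Cox model that Data analysis does not name. Nor can the counts in the illustration be weighed against the progression rates quoted in the Introduction, because the article does not say how those cohorts defined progression.

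What the reply does not remove is the contradiction. Reading the lead sentence as limited by criterion 3 protects against day-0 events only by excluding the elderly-range group, which three other parts of the article say will be followed or compared. Condensation does not explain this, because the conflicting statements are all printed.

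**Conclusion.** The eligibility contradiction is established on the face of the article. The abstract, the lead sentence of the criteria and criterion 3 give three populations, and criterion 3 excludes a group that the objectives need.

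Events at time zero are a conditional consequence. They can arise at ages 60-80 if the lead sentence governs without the abstract's cap. Under criterion 3 alone they need a new limit above 10, and under the abstract's cap they cannot occur. Their number is not derivable. The illustrative 4 to 54 of 438 (2 to 73 on wider assumptions) depends on assumed limits and a log-normal TSH, and is an overcount because of patients over 80.

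Severity is moderate. This is a contradiction to reconcile before analysis, not a proven bias in the central comparison.

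**What to change.** Reconcile all three statements so that the criteria define one population:

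1. Replace criterion 3 with TSH above the general-population upper limit and below the abstract's own 10 mIU/L at the qualifying measurement.
2. Classify enrolled patients as below or above the age-specific limit, instead of excluding those above it. Align the lead sentence with this. Adding the cap to criterion 3 while leaving its new-standard ceiling in place would not be enough, because the group above the new limit would still be excluded.
3. In Data analysis, exclude from the Cox risk set anyone who already meets a TSH endpoint component at baseline, that is, TSH ≥10 at ages 60-80. This covers a baseline value that differs from the qualifying one, and it can be applied to patients already enrolled.

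The treatment triggers need no change for this purpose. The cost is one line in the criteria and one in the analysis section, plus a smaller group above the new limit than an uncapped lead sentence would give.

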## Methods

### Research type

This study adopts the methodological strategy of the cohort study in analytical epidemiology to carry out various data collection, diagnostic test analysis around the gold standard and the test data of diagnostic subjects, and economic analysis.

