### Study population

We are conducting a prospectively observational study on patients over 60 years of age diagnosed with SCH. The study was conducted in the First Affiliated Hospital of China Medical University and the West China Hospital of Sichuan University. Patients will be included from December 2022 to December 2023, and the follow-up data will be collected until December 2025.

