### Data analysis

We will calculate age-specific TSH reference intervals based on the obtained data, analyze the natural outcomes, the occurrence of cardiovascular events, cognitive status, depression, and fatigue of elderly patients with SCH diagnosed under different reference intervals, and conduct economic analysis.

Continuous data will be expressed as mean ± standard deviation or median with a range of quartiles. Classification data will be expressed in numbers with percentages. Cox proportional risk model will be used to evaluate survival results. The variables measured several times during the follow-up period will be compared with the paired t-test according to the clinical management used. The significance level will be set to 0.05, and R software, prodlim, and Cairo software will be used to analyze the data.

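### Leaving the study midway is listed as an exclusion criterion, so the cohort as written is conditioned on completing follow-up and its results are open to selection bias of unknown direction

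*Protocol article*

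**What the plan says.** All references are to the Methods of the protocol article.

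- **Inclusion criteria and exclusion criteria.** Items (2) and (3) of the exclusion list read "Exit halfway due to various reasons.(3) Unable to cooperate with the project team to complete all inspection contents". They stand between the consent criterion and a list of other causes of raised TSH, both of which are ordinary entry conditions.
- **Research type.** "This study adopts the methodological strategy of the cohort study in analytical epidemiology".
- **Study population.** The study is described as prospective and observational. "Patients will be included from December 2022 to December 2023, and the follow-up data will be collected until December 2025".
- **Study follow-up assessments.** Patients "will be followed up every 6 months", each time with the full set of questionnaires, blood tests and two ultrasound examinations. When FT4 falls below the reference range, "follow-up is terminated and thyroid hormone replacement therapy will be initiated".
- **Data analysis.** "Cox proportional risk model will be used to evaluate survival results".

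No section says that patients who leave early, or who miss later examinations, stay in the analysis or are censored.

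**The concern.** An exclusion criterion should be decidable when the patient enters. Leaving midway is not: it is a future event, so using it to define the cohort means that membership depends on what happens during follow-up. Item (3) has the same effect if it is applied to the later visits.

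The main outcomes under Research objectives and main results include cardiovascular events, cognition, depression and fatigue. In patients aged 60 to over 80, illness, cognitive decline, low mood and death are plausible reasons for leaving or for failing to finish a long set of examinations. Selection on leaving may then be selection on the outcomes themselves. Every natural-outcome estimate would describe people who completed the study, not elderly patients diagnosed with SCH, and the diagnostic and economic conclusions rest on those estimates.

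**Working it through.** **1. Time at risk of being excluded.** Entry runs from December 2022 to December 2023 and follow-up ends in December 2025, so each patient is followed for 2 to 3 years. At one visit every 6 months that is about 2/0.5 = 4 to 3/0.5 = 6 follow-up visits at which items (2) or (3) could be triggered.

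**2. Stated figures.** The only relevant design figure is the sample size of 438. The article gives no effect size, power, precision or dropout for it, so it cannot be reproduced. The point does not depend on it.

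**3. Inputs for an illustration.**
- True progression p: 26.8% (the cited Spanish study, 6 years) and 3.4% (the cited Chinese study, 3 years), both from the Introduction. They serve only as a high and a low value.
- Exit proportion d: not given; assumed 10%, 20% and 30%.

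**4. Exit related to progression.** Let progressors leave with probability e1 and non-progressors with e0, where e1 = R × e0.

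e0 = d / (pR + 1 − p); observed p = p(1 − e1) / [p(1 − e1) + (1 − p)(1 − e0)]

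For p = 0.268, d = 0.20, R = 2:
- e0 = 0.20/1.268 = 0.1577 and e1 = 0.3155
- observed p = 0.268 × 0.6845 / 0.80 = 0.229

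With R = 0.5, e0 = 0.20/0.866 = 0.2309 and e1 = 0.1155, so observed p = 0.268 × 0.8845 / 0.80 = 0.296. With R = 1, observed p = p.

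**5. Exit independent of progression, event-free leavers deleted.** Take exponential event and exit times over 3 years, with d now the 3-year exit probability. For p = 0.268 and d = 0.20:
- 3-year hazards: −ln(0.732) = 0.3120 for progression and −ln(0.80) = 0.2231 for exit
- complete and event-free: 0.732 × 0.80 = 0.5856
- progress before leaving: [0.3120/(0.3120 + 0.2231)] × (1 − 0.5856) = 0.2416
- observed p = 0.2416/(0.2416 + 0.5856) = 0.292

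A simulation of the same set-up gave 0.2917.

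**6. Results.**

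| Scenario | True 26.8%; exit 10% / 20% / 30% | True 3.4%; exit 20% |
|---|---|---|
| Progressors leave twice as often | 25.1 / 22.9 / 20.2% | 2.6% |
| Progressors leave half as often | 28.1 / 29.6 / 31.7% | 3.8% |
| Exit independent, event-free leavers deleted | 27.9 / 29.2 / 30.7% | 3.8% |
| Equal exit probability in both groups | 26.8% throughout | 3.4% |

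**7. Precision.** If all leavers are removed, 438 falls to 438 × 0.90 = 394, 438 × 0.80 = 350 or 438 × 0.70 = 307.

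**The case against.** Several points on the other side have weight.

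- **Item (3) may be a screening rule.** Inability to cooperate can be judged at entry, and that would be a normal criterion in a study built on questionnaires and ultrasound. This stands: item (3) is ambiguous, not plainly wrong. It still needs a time point, because it refers to all examinations and directly follows an item that cannot be a screening rule.
- **The list may simply have absorbed withdrawal criteria.** The article is condensed, it nowhere says that accrued data are deleted, and a Cox model suggests that partial follow-up was meant to be used. That may be the intention, but it is not what the text says. An analysis plan that kept leavers would contradict the stated criteria.
- **The direction of bias.** A reader might infer that dropping leavers must understate risk and so favour the view that SCH in the elderly is over-diagnosed. With completers' risk over true risk equal to 1/(1 − d + dk), where k is the relative risk in leavers, d = 0.20 and k = 2 give 1/1.2 = 0.83. But k = 0.5 gives 1/0.9 = 1.11, and k = 1 gives no bias. The documents give neither d nor k, so they do not support a one-sided claim.
- **Low FT4.** A reader might also infer that patients whose follow-up stops at low FT4 would be excluded as non-completers. The Abstract names a fall in FT4 as an endpoint event in both age groups, so stopping there is reaching an endpoint. A clarifying sentence is enough.

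**Conclusion.** The concern holds for item (2), which is wrong as written, and for item (3) in so far as its timing is open. Together they condition the cohort on completion, contradict the prospective cohort design, and discard follow-up that the planned model could use.

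The size and direction of the bias are unknown. Under an assumed 20% exit, a true 26.8% could appear as about 22.9%, about 29.2% or unchanged, depending on how leaving relates to progression. The independent-exit case shows that deletion can distort the result even when leaving has nothing to do with progression; there, censoring would remove the distortion. Where leaving is related to outcome, censoring alone does not guarantee an unbiased estimate. It does keep these patients in the cohort, so that the problem can be seen and examined.

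**What to change.** 1. Delete item (2) from the exclusion criteria and restate it as a withdrawal rule.
2. Restrict item (3) to inability to complete the baseline assessments, judged before enrolment.
3. State that all enrolled patients stay in the analysis, censored at the last assessment for the endpoint concerned. The last thyroid test suits the thyroid endpoints but not cardiovascular events.
4. Use the questionnaire data that are available from patients who leave, and report reasons for leaving, including death.
5. State that reaching the low-FT4 endpoint counts as an event, not as an exclusion.
6. Keep a completers-only analysis as a sensitivity analysis at most.

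**Cost.** Changes to the criteria and analysis text, with no added visits or tests. Reasons for leaving, including deaths, must be recorded, and some incomplete records will have to be modelled. The change should be made before any leavers' records are set aside, since they may not be recoverable later.
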